**Methods::**

This is a multicenter, assessor-, and analyst-blinded, randomized controlled trial with 3 parallel arms: TN, PT, and TN combined with PT (Tuina combined with physiotherapy) group. Six hundred twelve eligible CNLBP patients will be randomly assigned to the groups in a 1:1:1 ratio in 3 centers. The TN intervention includes 9-step routine techniques, while the PT intervention includes a physiotherapy treatment plan based on a patient's symptoms. The interventions for both groups will last for 30 minutes and will be carried out for 6 sessions in 8 weeks. The primary outcome will be the visual analog scale pain score. And the secondary outcomes will include the Oswestry Disability Index, spinal range of motion, 36-item short-form health survey. Safety evaluation will be recorded during the whole study. All data in this randomized controlled trial will be analyzed by SAS 9.4.

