### Sample size calculation

2.7

This is a randomized controlled trial with 3 parallel arms. The test groups are the TN and T&P groups; the control group is the PT group. The visual analogue scale (VAS) score is the primary outcome. We use ANOVA to calculate the sample size. According to the previous report,^[24]^ the mean (standard deviation) difference of the VAS score of pre- and post-treatment in the TN group, T&P group, and PT group is 1.4 (0.8), 1.9 (0.9), and 1.65 (0.85), respectively. Assuming *α* = 0.05 (2-sided), *β* = 0.80, 171 subjects (57 subjects per group) are needed to achieve an 80% probability of detecting difference (PASS software, Ver. 11, NCSS, LLC. Kaysville, Utah; www.ncss.com). When considering a potential dropout risk of 15%, a total of 204 subjects (68 subjects per group) will be required as a sample size for statistically significant results at each center.

Stratified by 3 centers, the combined sample size is 612 for a meta-analysis.

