### Statistical analyses

2.16

The analysis set will consist of a full analysis set (FAS), a per-protocol set, and a safety set. The safety set will include randomly assigned participants and receive at least one intervention treatment. The FAS will consist of data indicating that the treatment was as close to the intention to treat as possible. In addition to meeting the safety set criteria, the participants must have been evaluated for the primary outcome at least once at the baseline. The FAS will be used in the primary analysis. For missing data, we will analyze the underlying reason and use an imputation adjustment approach, and the last observation carried forward analysis will be used to handle the missing data. After the primary analysis, a sensitivity analysis will be performed by comparing the results from the per-protocol analysis and the intention to treat analysis to evaluate the impact of missing data on the trial results. Besides, subgroup analyses by the center will be done.

(1)Statistical analysis methodFor all of the analyses, SAS version 9.4 was used. The confidence interval will be established at 95%, and the significance level at 0.05.Continuous variables were analyzed with an ANOVA test if normally distributed (results are presented as means ± SD) or Kruskal-Wallis H test if not normally distributed (presented as median with interquartile range). Multiple comparisons were addressed using the Tukey post hoc test (for ANOVA), and Bonferroni correction (for Kruskal–Wallis). The classification count data is checked by the chi-square test. This study used a one-sided test. When *P* < .05, the difference was considered statistically significant.(2)Statistical analysis contenta.Baseline evaluation: Social demographic characteristics, baseline severity analysis.b.Efficacy evaluation: We use the low back pain VAS score sheet, spinal ROM sheet, ODI scale, SF-36 scale, and the number of treatment sessions.c.Safety evaluation: Evaluation was made by the incidence of adverse events or recurrence of pain, or further injury from accidents during the follow-up period, and the level of safety.d.Compliance evaluation: Evaluation was carried out using the compliance rate.

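### Sections 2.7 and 2.16 disagree on whether the trial's inference rests on each centre, on a meta-analysis or on one pooled analysis, and the 612 is not derived from the analysis that section 2.16 describes

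*Protocol article*

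**What the plan says.** Section 2.7 sizes by analysis of variance ("We use ANOVA to calculate the sample size") on a mean (SD) pre-to-post VAS change that, in the "TN group, T&P group, and PT group is 1.4 (0.8), 1.9 (0.9), and 1.65 (0.85), respectively". At two-sided 5% it concludes that "171 subjects (57 subjects per group) are needed to achieve an 80% probability of detecting difference". After 15% dropout this becomes 204, which "will be required as a sample size for statistically significant results at each center". The total is then introduced in one sentence: "Stratified by 3 centers, the combined sample size is 612 for a meta-analysis".

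Section 2.16 assigns the primary analysis to the FAS and does not divide it by centre. Continuous outcomes are tested by ANOVA, or by Kruskal-Wallis if not normal, with Tukey or Bonferroni adjustment respectively. No centre term and no meta-analysis appear. On centre it says only: "Besides, subgroup analyses by the center will be done".

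The abstract describes a single trial, with patients "randomly assigned to the groups in a 1:1:1 ratio in 3 centers". Section 2.8 has each site run its own randomization by a common method.

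**The concern.** Section 2.7 treats the centre as a unit that should reach significance by itself and the 612 as material for combining three results. Section 2.16 treats the centre as a subgroup of one analysis and drops the combination. These are different analyses with different power and, if more than one were allowed to carry the conclusion, different error rates. A reader cannot tell which test the sample size serves.

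Two things are at stake. The first is how the result will be read: with centre, pooled and meta-analytic results all available and unranked, the choice of which to put forward could be made after they are seen. The second is the design. Randomization is run separately at each site, so centre is a stratum of the design, yet the analysis described leaves it out of the model.

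**Working it through.** **Inputs.** From section 2.7: means 1.4 (TN), 1.9 (T&P) and 1.65 (PT); SDs 0.8, 0.9 and 0.85; α = 0.05; 80% power; 15% dropout; three centres. Assumption: a common SD of 0.85. The root mean square of the three SDs is 0.851 and gives the same sample size.

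**1. The plan's own figures.** For a one-way ANOVA with n per arm, the noncentrality is λ = n·Σ(mᵢ − m̄)²/SD². Here m̄ = 1.65 and Σ(mᵢ − m̄)² = 0.0625 + 0.0625 + 0 = 0.125.
- n = 57: λ = 57 × 0.125/0.7225 = 9.86. With 2 and 168 degrees of freedom the power is 80.2%. At n = 56 it is 79.5%, so 57 per arm (171) is reproduced.
- Dropout: 57/0.85 = 67.06, rounded up to 68 per arm; 3 × 68 = 204 per centre.
- Total: 3 × 204 = 612.

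The arithmetic is right. It is a calculation for one centre, multiplied by three.

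**2. What those numbers give at each level**, under the assumed effect:

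| Reading | Calculation | Power |
|---|---|---|
| One given centre significant | λ = 9.86 | 80.2% |
| All three centres significant | 0.802³ | about 52% |
| At least one centre significant | 1 − 0.198³ | about 99% |
| One pooled ANOVA, 171 evaluable per arm | λ = 171 × 0.125/0.7225 = 29.6; 2 and 510 df | about 99.9% |

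If significance at each centre were the aim, the design would achieve it about half the time. If the pooled FAS analysis is the aim, the omnibus test on these assumptions is far above the 80% target, so the 612 did not come from it.

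**3. Type I error, conditional on a rule that the article does not state.** Suppose any significant centre counted as success, each tested at 5% with no true effect.
- Three centres: 1 − 0.95³ = 14.3%.
- Any centre or the pooled test: about 16.5% (null simulations with 3 centres × 3 arms × 57 gave 16.2% to 16.5%).

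**4. The meta-analysis, whose model is not named.** Take one unadjusted pairwise difference of 0.25 (PT against either other arm), SD 0.85 and no true heterogeneity. The standard error per centre is 0.85·√(2/57) = 0.159; combined over three centres it is 0.159/√3 = 0.092.
- Fixed-effect combination: about 78%, the same as a pooled comparison with 171 per arm.
- DerSimonian-Laird random effects, z test: about 68%.
- Hartung-Knapp, t with 2 degrees of freedom (critical value 4.303): about 34%.

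The model alone moves power from about 34% to about 78%.

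**The case against.** Much can be said for the plan. Section 2.16 does name a primary analysis, on the FAS, and section 2.11 fixes one primary outcome. Tukey or Bonferroni adjustment is stated, and calling the centre results subgroup analyses places them below the primary one. A reader might infer that the trial has no protected primary test; the text does not support that. What is missing is narrower: the adjustments are attached to the ANOVA and Kruskal-Wallis tests, and nothing covers the centre, pooled and meta-analytic levels together.

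A reader might also infer from section 2.7 that one significant centre would make the trial positive, with an error rate of 14% or more. No passage says so. The phrase about each centre explains how many patients a centre needs and does not define success. The error rates in step 3 are therefore hypothetical. So is the 52%, in the sense that no passage requires all three centres to be significant.

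Nor does the word meta-analysis mean that power would be lost. The 34% belongs to one random-effects method that the article never chooses. With three equal centres, a fixed-effect combination keeps 78% and is nearly the same analysis as a pooled model with centre as a fixed effect. These are also unadjusted pairwise figures: under the plan's Tukey procedure, pooled power for a 0.25 difference is about 64%.

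Finally, this is a condensed article, and the form of the model or a testing order may stand in the full protocol or SAP. That would excuse silence. It does not excuse two sections of the same article that give the 612 and the centres different roles.

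**Conclusion.** The point holds as a contradiction within the article. Section 2.7 sizes each centre for its own significant result and the total for a meta-analysis; section 2.16 performs neither as its primary analysis. No order or error control is stated across the three levels, and centre is absent from the model although each site randomizes independently.

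The size: about 80% omnibus power for one centre, about 52% for all three together and about 99.9% for a pooled test, assuming a common SD of 0.85, the stated means in every centre and 57 evaluable per arm per centre. The sample size arithmetic is correct, and the trial is not underpowered for the pooled omnibus test. The inflated error rates apply only if centre results were allowed to count as success, and the loss of power only under some meta-analysis models. Both are reasons to close the gap in wording; neither is a demonstrated fault of the plan. This should be corrected before the data are analysed. No interim analysis is planned, so the change need not be made in the light of results.

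**What to change.** In section 2.16, name one primary analysis: an individual-patient analysis of VAS change over the two-month treatment in all FAS patients from the three centres, with centre as a fixed effect, at two-sided 5% as in section 2.7. An equivalent fixed-effect, centre-stratified combination would also serve if the sponsor prefers to keep the idea of combining centres, but it must then be named with its model.

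In section 2.7, delete the phrase about significant results at each centre, replace the reference to a meta-analysis with the named analysis, and restate the power of the 612 against it. Say whether that power refers to the omnibus test or to the adjusted pairwise comparisons, because on the same inputs these differ widely (about 99.9% against about 64% for a 0.25 difference under Tukey).

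Report centre results as supportive estimates with confidence intervals and a single treatment-by-centre interaction test.

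The cost is a wording amendment to two sections, with the ethics submission and registry entry that the article already foresees for amendments. The number of patients and the data collected do not change. The downside is that no centre can present its own result as confirmatory.

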### Randomization

2.8

In this study, we will use a blocked randomization method. Each site will run the randomization independently, and the same randomization method will be adopted. A statistician will use SAS 9.4 (SAS Institute Inc., Cary, NC) with a “proc plan” program to produce the randomizing scheme. After production, the scheme will be signed and sealed by the staff who produces it and kept by other staff participating in this trial. It will not be allowed to be checked by anyone except the Principal Investigator. Physicians in each center will be responsible for getting random numbers.

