### Blinding

2.9

Due to the inability to blind patients, the practitioners, physiotherapists, and patients are not blinded.

The assessment of clinical efficacy will be performed by a clinical assessor who will be masked to the treatment assignment. The clinical researcher, assessor, and statistician do not share study information during this clinical trial.

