### Data collecting and monitoring

2.14

All baseline assessment, end of 2-month intervention, 3 months post-intervention data will be collected by the CRC blind to the treatment modality or treatment groups. All subjects’ adverse events and additional treatment during the follow-up period will also be recorded.

This trial uses a paper-based case report form (CRF) and an electronic data management system. All data will be recorded by CRC in CRFs. Completed CRFs are reviewed by Clinical Research Associate (CRA), from a third-party company, independent of the research team and blinded to group allocation. All data administrators have data analysis qualifications and are trained uniformly. To ensure the accuracy of the data, 2 data administrators independently enter the information and proofread it. If there are issues with the information in the CRF, the CRA can fill out a query sheet and give it to the CRC and site PI. The CRC can then modify the data according to any revisions made by the site PI. After confirming that the database is correct, the site PI, CRC, and statistician will lock the database.

All documents that contain participants’ personal information will be identified by code number and stored separately. Only researchers involved in this study can be available to the confidential documents.

All study data, including the paper-based documents and electronic data, will be stored at each site for 5 years after the completion of the trial.

Because the study is not a drug trial and the sponsor or funder has no access to the raw data, a data monitoring committee will not be formed, and there is no planned trial audit. Besides, there are no interim analyses and stopping guidelines due to the very low risks of adverse events and other unintended effects.

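### The Principal Investigator may check the randomisation scheme at any time and trial staff hold it, so allocation concealment is not assured with respect to the PI, who is nowhere stated to be blinded

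*Protocol article*

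**What the plan says.** Section 2.8 (Randomization) describes blocked randomisation, run site by site: "Each site will run the randomization independently, and the same randomization method will be adopted". A statistician generates the scheme in SAS. Then "the scheme will be signed and sealed by the staff who produces it", and it is "kept by other staff participating in this trial". On access the section says: "It will not be allowed to be checked by anyone except the Principal Investigator". On obtaining an allocation it says: "Physicians in each center will be responsible for getting random numbers".

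Section 2.9 (Blinding) says that "the practitioners, physiotherapists, and patients are not blinded", and that efficacy assessment is "performed by a clinical assessor who will be masked to the treatment assignment". The PI is in neither group.

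Section 2.14 (Data collecting and monitoring) has all data entered on case report forms by a clinical research coordinator (CRC) who is blind to group. A blinded third-party clinical research associate (CRA) reviews the forms and may raise a query to the CRC and the site PI. After that, "The CRC can then modify the data according to any revisions made by the site PI". The site PI, the CRC and the statistician together lock the database.

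**The concern.** Allocation concealment requires that nobody able to influence enrolment can learn the next assignment before a patient is committed to the trial. A written permission for the PI to look at the scheme opens that barrier for one senior role. Custody by people who work in the trial adds a second, weaker doubt, since nothing says that the custodian is separate from recruitment or treatment.

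The same role appears to decide the answers to data queries. The primary outcome is change on a 100 mm pain scale, which is subjective, and the trial describes itself as assessor- and analyst-blinded. If allocation were known at enrolment, prognosis could differ between arms through selection. If it were known when a query is answered, a correction could be coloured by treatment. Analysis cannot reliably repair either problem afterwards.

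**Working it through.** No arithmetic applies. The question is who may know the allocation, when, and what that person then decides. All section numbers are from the protocol article.

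**Step 1: access to the scheme (2.8).**
- Produced by: a statistician, who signs and seals it.
- Held by: other staff taking part in the trial.
- May be checked by: the Principal Investigator only.
- Reason, trigger or time limit for checking: none given. Access is not confined to the period after enrolment or after database lock.

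This is a stated rule, not a detail left to a fuller document. The seal works against everyone except the one role that is allowed past it.

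**Step 2: is there a need for access (2.9)?** The usual reason for early access is emergency unblinding. Here patients, practitioners and physiotherapists already know the treatment, so a safety decision does not require the scheme. No other purpose is stated.

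**Step 3: is the PI blinded (2.9, 2.14)?**
- Stated as masked or blind: the assessor, the CRC and the CRA.
- Stated as not blinded: practitioners, physiotherapists and patients.
- Not stated: the PI.

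Section 2.9 also bars the clinical researcher, the assessor and the statistician from sharing study information, but it does not name the PI.

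**Step 4: what the PI decides (2.14).** The case report forms hold all data, so outcome data are included. After a CRA query, the CRC changes data according to the site PI's revisions. The site PI is one of three parties to the lock.

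**Step 5: are the two titles one person?** Section 2.8 says Principal Investigator and section 2.14 says site PI. Each site runs its own randomisation, and section 2.15 (Quality control) mentions only the PIs of the three research centres, with no separate overall PI. Identity is likely, but the text does not state it. If they are different people, the point about the scheme still stands on section 2.8 alone.

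**Result.** Sections 2.8, 2.9 and 2.14 contain nothing that prevents a PI from knowing upcoming allocations. If the titles coincide, nothing prevents that PI from also deciding data revisions before lock.

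**The case against.** The protocol has real safeguards. The scheme is sealed and closed to everyone but the PI. The assessor and the CRC are blind, the CRA is blind and external, and data are entered twice independently. Revisions follow a CRA query, so section 2.14 gives the PI no general licence to edit, and having the investigator answer queries is ordinary practice. Section 2.3 (Participants and recruitment) has a trial communicator or research assistant screen patients, and section 2.8 has physicians obtain the numbers. No section says that the PI enrols anyone. The custodian is distinct from the producer and is not said to recruit, treat or assess.

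All of this stands, and it limits the point. A reader might infer that neither concealment nor blinded data correction is protected at all, or that recruiters know every coming assignment. The documents do not support that: section 2.8 closes the scheme to recruiters unless the PI is one of them, and permission to look is not evidence of looking.

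A reader might also infer that allocations can be guessed from earlier ones within a block. The article gives no block size, and block sizes and the mechanics of releasing each allocation are details that an article may leave to the full protocol. That reading is not pursued.

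One more objection is sound. Because treatment is delivered openly, a site PI could learn allocations without the scheme, so closing it would not blind the person who answers queries. The data-revision part therefore needs its own remedy.

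What the objection does not remove is the exception itself. The seal does not bind the PI, the blinding of assessor, CRC and CRA protects data collection and not enrolment, and double entry protects transcription only.

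**Conclusion.** The point holds in limited form. Section 2.8 allows the PI to check the scheme without reason or time limit and leaves it with staff of the trial, so allocation concealment is not assured with respect to the PI. Section 2.14 gives the site PI the decision on revisions after queries and a part in the lock, and no section states that the PI is blinded.

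No size of bias can be derived from the documents, and none is claimed. The judgement rests on two things: reading the exception as it is written, without an unstated restriction, and, for the data-revision part only, the inference that the Principal Investigator and the site PI are the same person. It assumes no misuse. The change is worth making because the exception has no stated benefit, its possible harm cannot be undone in analysis, and removing it is cheap.

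**What to change.** - In section 2.8, delete the PI exception. State that the scheme is closed to all PIs and site staff until database lock.
- Name a custodian with no role in recruitment, treatment, assessment or the blinded analysis. Custody should not pass to the statistician who does the analysis, because that could undercut the analyst blinding that the trial claims.
- In section 2.14, require every site PI revision of outcome data to be supported by source documents and recorded in an audit trail. This works whether or not the PI knows the allocation.

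The cost is a change of custodian, some documentation of revisions, and an amendment while recruitment is under way (section 2.2 gives December 2020 to December 2022). Under section 2.15 the amendment goes through the steering committee to ethics approval, and section 2.2 lists three such approvals. It can protect only patients not yet randomised. For those already enrolled, the trial can record whether any PI has opened the scheme.

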### Blinding

2.9

Due to the inability to blind patients, the practitioners, physiotherapists, and patients are not blinded.

The assessment of clinical efficacy will be performed by a clinical assessor who will be masked to the treatment assignment. The clinical researcher, assessor, and statistician do not share study information during this clinical trial.

